### Data Management

Data will be collected in the Emergency and Trauma Research Centre, University of Insubria, Varese, Italy by clinical data technicians on an electronic case report form, using double password-protected computers. Prespecified lists, ranges of values, and drop-down menus in the electronic case report form will facilitate data entry and prevent writing errors. Study documents will be deidentified and stored in the Emergency and Trauma Research Centre, University of Insubria, Varese, Italy. All personnel involved in data analysis will be masked. Only the principal investigators and statisticians will have access to the final data set.

### Confidentiality

People with direct access to the data will take all necessary precautions to maintain confidentiality. All data collected during the study will be rendered anonymous. Only initials and inclusion numbers will be registered.

### Plans for the Collection, Laboratory Evaluation, and Storage of Biological Specimens

On day 0, blood samples (15 mL) will be drawn in EDTA tubes, centrifuged, and stored (−80°C) for subsequent analysis. After the first analysis, the remaining biological specimens will be kept for a maximum duration of 15 years.

### Statistical Methods for the Primary and Secondary Outcomes

Associations between different variables will be examined using Pearson correlation coefficients. Paired comparisons will be made using the Wilcoxon matched pairs test. Nonpaired comparisons will be made using the 2-tailed Mann-Whitney test. Multiple comparisons will be made using appropriate one-way analysis of variance (ANOVA). A *P* value <.05 will be considered statistically significant. All statistical analyses will be performed using R version 3.4.3 (R Project for Statistical Computing) and SPSS 21 (SPSS Inc).

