#### Secondary Endpoints

The secondary endpoints are to correlate clinical data and vaccination history with laboratory immune patterns to identify protective factors for severe COVID-19 and break new ground for advanced therapeutic strategies.

Identifying differences between patients having mild infection with positive outcomes and patients having ARDS requiring ventilatory assistance could be useful to optimize the therapy and to come up with an immunostimulant therapy that can produce specific immunity and can decrease the hyperactivity of the innate response and thus the inflammatory condition.

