### Recruitment

The proposed study aims to analyze patients with confirmed SARS-CoV-2 infection by real-time reverse transcription polymerase chain reaction (RT-PCR) assays on throat swabs in order to identify differences in their immune responses. Patients will be recruited at the Emergency Department of “Ospedale di Circolo – ASST Sette Laghi,” University of Insubria in Varese, Italy.

A control group of healthy people will be required for further comparison of the findings. We will consider healthy people (both males and females; aged ≥18 years) without infection (negative for SARS-CoV-2), without symptoms of infectious diseases (neither chronic nor acute), and without chronic pathologies (N=30).

After the informed consent procedure, the sample will be divided into 4 subgroups according to the severity of clinical impairment, with at least 30 people in each subgroup. The severity of pneumonia cases will be measured with SMART-COP (systolic blood pressure, multilobar chest radiography involvement, albumin level, respiratory rate, tachycardia, confusion, oxygenation, and arterial pH) [30-32]. The following 4 categories of patients positive for SARS-CoV-2 infection will be analyzed: (1) asymptomatic patients (AS19); (2) mildly symptomatic patients with fever, tiredness, dry cough, diarrhea, etc and without full-blown pneumonia (PAU19); (3) patients with a diagnosis of pneumonia with a “low” risk score (SMART-COP) (POL19); and (4) patients with a diagnosis of pneumonia with a “moderate/high” risk score (SMART-COP) (ARD19).

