### Preparation of Plasma and Isolation of PBMCs From Blood

From different groups of patients, blood samples (10-15 mL) will be drawn in EDTA tubes and centrifuged at 360 *g* for 10 minutes to obtain plasma that will be stored at −80°C for subsequent analysis of cytokines and chemokines of interest by enzyme-linked immunosorbent assay (ELISA) (IL-1β, IL-6, TNFα, IFNα, IL-10, IL-12, CCL2, and CXCL10) at the end of enrollment.

The cell pellets will be brought back to the initial volume with phosphate-buffered saline (PBS) (Euroclone) and diluted 1:1 (v/v) with PBS. It will then be subjected to density gradient stratification with Lymphosep (Biowest) at 500 *g* for 30 minutes at room temperature with no brake. The PBMCs derived from the white ring will be collected, washed twice in PBS, and then used for subsequent experiments using a flow cytometer assay [25]. The in vitro culture using PBMCs can vary from ex vivo 1 day to a few days, and cells will be maintained in RPMI 1640 medium (Euroclone), supplemented with 10% fetal bovine serum (FBS) (Euroclone), 2 mM l-glutamine, and 100 U/mL penicillin and 100 μg/mL streptomycin (both Euroclone), at 37°C and 5% CO_2_.

To perform ex vivo flow cytometry cell phenotype analysis, 2.5×10^5^ fresh or frozen total PBMCs per tube will be stained for 30 minutes at 4°C with monoclonal antibodies (mAbs) (Becton Dickinson [BD]) as follows: CD3-BB700, CD56-APC, CD16-PE-Cy7, CD159a (NKG2A)-BV510, NKG2C-PE, NKGD2-PE, DNAM-1-PE, CD25-PerCP-Cy5.5, CD69-PE, CD279 (PD1)-BUV737, TIGIT-BV786, CD96-BB515, and CD366 (TIM3)-BV421. Samples will be acquired using BD LSR Fortessa. Following the forward/side scatter setting, NK cells will be divided into 2 cell subsets (ie, CD3^−^ and CD56^dim^ CD16^+^ cells [CD56^dim^ NK cells, the major subset, about 90%] and CD3^−^ and CD56^bright^ CD16^−/low^ cells [CD56^bright^ NK cells, the minor subset, about 10%]). Other marker expressions will be evaluated in both subsets of gated cells.

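### Pearson correlation and one-way ANOVA on untransformed values sit beside rank tests for the same markers; if the markers are clearly skewed, this loses power and lets single extreme values drive correlations

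*Protocol article*

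**What the plan says.** The section Statistical Methods for the Primary and Secondary Outcomes names four methods:

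- Associations: "Associations between different variables will be examined using Pearson correlation coefficients".
- Paired data: "Paired comparisons will be made using the Wilcoxon matched pairs test".
- Two independent samples: "Nonpaired comparisons will be made using the 2-tailed Mann-Whitney test".
- More than two groups: "Multiple comparisons will be made using appropriate one-way analysis of variance (ANOVA".

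The significance threshold is .05. The section mentions no transformation and no rank alternative to Pearson or ANOVA, and it does not assign a test to any particular variable.

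The laboratory section lists the plasma proteins to be measured by ELISA: "IL-1β, IL-6, TNFα, IFNα, IL-10, IL-12, CCL2, and CXCL10". The Primary Endpoint section foresees very large cytokine release in severe cases. Under Recruitment, "the sample will be divided into 4 subgroups according to the severity of clinical impairment". The Secondary Endpoints section sets out to "correlate clinical data and vaccination history with laboratory immune patterns".

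**The concern.** For two samples, the plan chooses tests that do not depend on the shape of the marker's distribution. For associations and for several groups, it names methods that work on raw means and products, and it gives no reason for the difference. The same cytokine would be ranked when two severity groups are compared and averaged on its raw scale when four or five are.

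This matters if a marker has a long right tail, which is plausible for concentrations expected to be very high in the sickest patients. Two things are then at stake. Real associations and group differences may be missed, and a Pearson coefficient may reflect one or two patients rather than the sample.

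**Working it through.** **The plan's own figure.** The Sample Size section says 30 per group can show differences of 20% to 30% in the phenotype and function of immune cells. It gives no SD and no power, so the figure cannot be reproduced. At 80% power (assumed) and two-sided .05, 30 per group detects 0.723 SD. The SD would then have to be 20/0.723 = about 28% of the mean, or 30/0.723 = about 41%. This says nothing about cytokine skewness.

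**Inputs.** From the documents: n=120 patients, groups of 30, 30 controls, alpha .05. Assumed: log-normal markers with log-SD s = 0.5, 1.0 or 1.5, and the effect sizes below.

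**Correlation.** Let both variables be log-normal with correlation 0.3 on the log scale. The correlation on the raw scale is (exp(0.3s²) − 1)/(exp(s²) − 1):

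- s=0.5: 0.0779/0.2840 = 0.27
- s=1.0: 0.3499/1.7183 = 0.20
- s=1.5: 0.9640/8.4877 = 0.11

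Pearson on raw values therefore estimates a weaker association as skewness grows. Ranks do not change under a log transformation, so Spearman's power does not depend on s.

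**Several groups.** Five groups of 30 are given log-scale shifts rising evenly to 0.75 SD, in steps of 0.75/4 = 0.1875 SD.

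Simulated power (about 3,000 runs per cell, so roughly ±2 points; repeat runs put the first ANOVA entry between 63% and 66%):

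| log-SD | Pearson | Spearman | ANOVA | Kruskal-Wallis |
|---|---|---|---|---|
| 0.5 | 85% | 89% | 63% | 69% |
| 1.0 | 58% | 89% | 47% | 69% |
| 1.5 | 39% | 90% | 27% | 70% |

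**Sensitivity to the assumptions.**

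- Only one variable skewed (n=120, latent correlation 0.253, Spearman 76%): Pearson has 75%, 63% and 46% at log-SD 0.5, 1.0 and 1.5.
- Inverse association of −0.3, both variables skewed: Pearson has 85%, 48% and 5%, against 89% to 90% for Spearman.
- Four groups of 30, graded effect set to about 80% power on the log scale: ANOVA has 73%, 56% and 36%, against 77% to 78% for Kruskal-Wallis.
- Only the most severe of five groups shifted, log-SD 1.0: ANOVA has 70%, Kruskal-Wallis about 81%, and an ordered-trend test about 69%.
- Near-normal markers: Pearson and ANOVA are 2 to 6 points better than the rank methods.

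**False positives.** With no true effect, skewness alone leaves Pearson at 4.5% to 5.6% rejection and makes ANOVA conservative, at 3.1% to 4.4%.

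**One extreme value.** Put one patient at k SD on both of two otherwise unrelated variables. Roughly, r = c/(c + n − 2), with c = k²(n − 1)/n. For k=6:

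- n=30: c = 36 × 29/30 = 34.8, so r = 34.8/62.8 = 0.55. Simulated: median r 0.56, 98% rejection; Spearman rejects in 6%.
- n=120: c = 36 × 119/120 = 35.7, so r = 35.7/153.7 = 0.23. Simulated: median r 0.23, 78% rejection; Spearman rejects in 5%.

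**The case against.** The strongest reply is that this is a condensed article. Transformations and distribution checks are usually left to the full protocol or analysis plan, and the word appropriate before ANOVA leaves room for a transformed or rank-based version. This stands in part for ANOVA. It does not cover Pearson, which is named without qualification. The inconsistency also lies in what is stated, not in what is left out.

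A second reply is that the documents never say the markers are skewed. That stands, and it makes the size of the loss conditional. For cell percentages in particular, a reader might infer right skew throughout. The laboratory section puts the main NK subset and the classical monocytes at about 90% each, and values that close to an upper limit do not look like a log-normal. The simulated losses are best read as applying to cytokine concentrations.

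A reader might also infer that Pearson is prescribed for yes/no vaccination data. The text assigns no test to vaccination history and does not say how it is coded, and the Mann-Whitney test is available for such a contrast. With a binary variable, Pearson gives the same p-value as the pooled t-test, so it would not be invalid.

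Finally, since the severity groups are ordered, a trend test might seem the obvious main analysis. ANOVA on ordered groups is valid, and the Primary Endpoint section speaks of severe patients rather than of a steady gradient. If only the most severe group differs, the trend test does worse than Kruskal-Wallis (about 69% against 81% at log-SD 1.0).

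**Conclusion.** The point holds as a conditional one. The plan treats the same markers by ranks in two-sample comparisons and by raw-scale methods elsewhere, without a stated reason.

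Under the assumed log-normal model, with both variables skewed for the correlation and a graded effect for the groups, the loss runs as follows from log-SD 0.5 to 1.0 to 1.5:

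- Pearson against Spearman: 89 − 85 = 4, 89 − 58 = 31 and 90 − 39 = 51 points.
- ANOVA against Kruskal-Wallis: 69 − 63 = 6, 69 − 47 = 22 and 70 − 27 = 43 points.

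The correlation loss is smaller if only one variable is skewed. It would go too far to say that a large loss is certain: the documents give no log-SD, and at 0.5 the loss is minor. It would also go too far to say that skewness inflates false positives or that outliers drive the ANOVA. The demonstrated outlier problem is specific to Pearson and needs a value that is extreme on both variables.

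**What to change.** In the statistical methods section:

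- Associations: Spearman, or Pearson on log-transformed values.
- More than two groups: Kruskal-Wallis, or ANOVA on log-transformed values.
- Optionally, add an ordered-trend test across the four severity groups as a supplementary analysis, not as the main test.

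This matches the rank tests already chosen and changes wording only, with no added patients, samples or assays. The Results section says the immunological analysis is still under way, so the choice should be written down before the marker results are examined. The cost is about 2 to 6 points of power for rank methods if the markers turn out near normal.

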## Introduction

### Background and Rationale

Coronaviruses are common human and animal pathogens. During epidemics, they cause up to one-third of community-acquired upper respiratory tract infections in adults and probably play a role in severe respiratory infections in both children and adults. However, coronaviruses are responsible for a limited amount of diagnosed pneumonia and acute severe illness, especially in the younger population, and a coinfection is frequently detected in hospitalized patients. Usually, the infection is responsible for mild-to-moderate symptoms that rapidly and spontaneously resolve [1].

The new strain of coronavirus, SARS-CoV-2, belongs to the beta-coronavirus family, and it shares all community-acquired coronavirus transmission routes and symptoms. However, the transmission rate is significantly higher, with a faster viral spread responsible for the worldwide outbreak.

In fact, it is a novel virus that was most likely recently passed from bats to humans, and consequently, it is almost unknown to the human immune system. Besides, SARS-CoV-2 seems to undergo modification rapidly during its spread, further avoiding immune defenses [2].

A higher mortality rate characterizes the novel coronavirus, and it has reached over 3% [3]. The death rate is over 1% only for patients aged over 50 years, and it is under 0.4% until 40 years of age. No fatalities have been declared among children under 10 years of age. Furthermore, the death rate is almost double for males when compared with females [4].

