However, several mechanisms of trained immunity remain unclear, because the trained immune memory–like phenomenon appears to be for a few months or at least a few years. This immunity is not persistent but progressively fades out. Decreased immune response in the elderly could be responsible for more severe acute respiratory disease from coronaviruses in general and higher mortality from COVID-19, since SARS-CoV-2 can cause an explosive attack against the respiratory system, which is similar to major trauma and allows the development of acute respiratory distress syndrome (ARDS). No evident differences were found in different age groups among healthy people, which could justify the drop in immunity against coronaviruses, except its natural fadeout. The trained immune response acts from the age of 2 years, when hypothetical stimulation occurs, to the fifth decade because of its slow decrease.

Vaccines provide external stimulations in healthy people that trigger immune system responses (eg, diphtheria, tetanus, and pertussis [DTP] vaccines stimulate the immune system). Specific vaccines trigger specific immune actions against specific infectious agents, but provide sprouting immunity against antigens in transit, such as those of coronaviruses and other community-circulating viruses [6]. The underlying immunological phenomena are “bystander effect” and “trained immunity.”

Children receive vaccines during the first year of life. Consequently, they become protected against not only specific pathogens but also multiple antigens from pathogens in transit. The developed immunity gives protection against multiple viral infections for years until naturally fading out. After the fifth decade, this immunity is slower to be recalled and reactivated. At this point, a viral infection will find the immune system almost incompetent, and the virus can enter the organism and cause extensive damage. Among elderly people, severe pneumonia and ARDS are frequently noted when they have a coronavirus infection, flu, etc. The history of pandemic viruses reveals an unexplained phenomenon, which could support this hypothesis. In fact, the “Spanish flu” showed a higher mortality rate among young people, especially those aged 20 to 45 years, which could be partly explained by their life conditions after the end of the First World War.

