#### Secondary Objectives

The secondary objectives are to identify protective factors, using anamnestic data, such as preceding vaccinations, comorbidities, clinical presentation of COVID-19 in terms of clinical signs and symptoms, and biochemical findings. The recognition of a population of patients safe from excessive inflammation against SARS-CoV-2 could define a risk score for the severity of COVID-19, which could allow for the best clinical choice tailored to each patient. Moreover, favorable immunological pattern identification could be followed by implementation of prophylactic or therapeutic immunomodulatory treatments.

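### The named between-group and association methods are all unadjusted, so the protective-factor inferences and the patient-control contrasts cannot be separated from age, sex and comorbidity

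*Protocol article*

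**What the plan says.** The section Statistical Methods for the Primary and Secondary Outcomes gives four methods. Three of them serve comparisons between groups and associations:

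- "Nonpaired comparisons will be made using the 2-tailed Mann-Whitney test"
- "Multiple comparisons will be made using appropriate one-way analysis of variance (ANOVA"
- "Associations between different variables will be examined using Pearson correlation coefficients"

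The fourth, the Wilcoxon matched pairs test, is for paired data. A P "value <.05 will be considered statistically significant". No regression, ANCOVA, stratified or matched analysis appears anywhere in the article.

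Under Recruitment and Sample Size, patients are placed in four categories by clinical severity (AS19, PAU19, POL19, ARD19), with 30 in each. The 30 controls are adults of either sex, from 18 years up, "without symptoms of infectious diseases (neither chronic nor acute), and without chronic pathologies (N=30". No age or sex matching is described. Under Eligibility Criteria, patients are excluded only for consent reasons or for HIV, hepatitis B or hepatitis C infection, so they may have other chronic disease.

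Background and Rationale ties age to outcome ("The death rate is over 1% only for patients aged over 50 years, and it is under 0.4% until 40 years of age"), says that severe illness is nearly absent under 40, and reports about twice the death rate in males. Of trained immunity it says: "This immunity is not persistent but progressively fades out". Pathophysiological Considerations adds that the NK share of lymphocytes depends on age. The Secondary Objectives are nevertheless to "identify protective factors, using anamnestic data, such as preceding vaccinations, comorbidities", and they look ahead to a risk score for severity.

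**The concern.** The article's own premise is that age is linked both to how severe the disease becomes and to the state of the immune cells being measured. Groups formed by observed severity can then be expected to differ in age, and a marker that depends on age will differ between them even if severity adds nothing.

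Vaccination is described as an early-life exposure whose effect fades, so time since vaccination is tied to age as well. A pairwise association between vaccination history and severity, or between vaccination and an immune pattern, cannot tell a vaccine effect from an age effect.

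The control group adds a second difference. Controls are chosen to be free of chronic disease and patients are not, so a patient-control contrast mixes COVID-19 with age, sex and comorbidity.

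At stake is the secondary objective, which is meant to inform a risk score and treatment choice, and any statement about how patients differ from healthy people because of COVID-19.

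**Working it through.** **The plan's own figure.** Sample Size says that 30 per group can show differences of 20% to 30%. No SD, coefficient of variation (CV) or power is given, so this cannot be reproduced. At two-sided 5% and 80% power the detectable standardised difference is (1.960 + 0.842) × √(2/30) = 0.72. The claim would therefore need a CV of about 0.20/0.723 = 0.28 for 20%, or 0.30/0.723 = 0.41 for 30%. This does not settle the adjustment question either way.

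**Inputs.** From the article: 30 per group, 120 patients, 30 controls, alpha 0.05 and the three unadjusted methods. Assumed, because the article gives no figures: age SD 15 years in each group, age gap between groups 0 to 30 years, and within-group marker-age correlation r of 0.2, 0.3 or 0.5.

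**Two groups.** Marker = r × age/15 + √(1 − r²) × noise, with no group term. The group difference carried by age alone is d = r × gap/15 SDs; for example 0.3 × 20/15 = 0.40. Rejection rates over 3,000 simulated trials per setting:

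| Age gap (years) | Mann-Whitney, r = 0.2 | r = 0.3 | r = 0.5 | Linear model with age, range over r |
|---|---|---|---|---|
| 0 | 4.7% | 4.5% | 4.5% | 4.8% to 4.9% |
| 10 | 7.9% | 10.7% | 22.8% | 4.8% to 5.4% |
| 15 | 11.0% | 20.6% | 44.4% | 4.9% to 5.3% |
| 20 | 15.8% | 30.5% | 68.5% | 4.4% to 5.6% |
| 30 | 31.3% | 60.6% | 95.9% | 5.1% to 5.8% |

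The Monte Carlo standard error near 5% is √(0.05 × 0.95/3000) = 0.4 percentage points.

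**Five groups** (controls and four severity categories, mean ages evenly spaced over a 20-year range, 1,500 runs). One-way ANOVA rejects in 12.9%, 23.7% and 63.3% for r = 0.2, 0.3 and 0.5. With age added the rates are 4.9%, 4.1% and 4.5%.

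**Pearson, 120 patients.** If two variables are related only through age, their correlation is the product of their correlations with age. The rejection probability follows from atanh(ρ) × √117.

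- Correlations with age of 0.5 and 0.3: ρ = 0.15, 0.151 × 10.82 = 1.63, significant in 37%.
- Correlations with age of 0.5 and 0.5: ρ = 0.25, 0.255 × 10.82 = 2.76, significant in 79%.

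**Cost of adjustment.** The variance of the group contrast is inflated by 1 + (gap/15)²/4, which gives 1.11, 1.25, 1.44 and 2.00 at gaps of 10, 15, 20 and 30 years. Part of this is recovered because age explains residual variance. At a 20-year gap the net factor is 1.44 × (1 − 0.25) = 1.08 for r = 0.5 and 1.44 × (1 − 0.04) = 1.38 for r = 0.2.

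**The case against.** Several points on the other side stand.

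- The Primary Objective is exploratory: to characterise phenotypes and activity across severities. An unadjusted comparison answers that as description. In the simulation the marker distributions truly differ once ages differ, so Mann-Whitney is right to reject its own null. The excess counts as error only if the question is a difference beyond age. That is what the protective-factor aim needs and what the descriptive aim does not.
- A reader might infer that the immune patterns found will be artefacts of age. The article gives no group ages and no marker-age correlations, so that cannot be said. A reader might also infer that the age imbalance is built into the design. It is not: groups are set by symptoms, pneumonia and SMART-COP, whose components as listed under Recruitment do not include age. Imbalance is expected, not guaranteed.
- The 4% to 6% result comes from fitting the model that generated the data. It does not cover non-linear age effects or skewed markers, and sex and comorbidity were not simulated.
- The Wilcoxon test is not affected. Within-person comparisons, such as the three time points in vaccinated staff, are not confounded by baseline age.
- The article links cytomegalovirus (CMV) to the risk profile but does not say that it changes NK cells, so the point does not rest on that.

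What does not stand is that adjustment is merely left to a fuller plan. The section names the methods for both primary and secondary outcomes, and none of those named can make the separation.

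**Conclusion.** The concern holds for three uses of the data: identifying protective factors, relating vaccination history to severity or immune patterns, and contrasting patients with healthy controls. With the named methods, none of these can be separated from age, sex and comorbidity. It does not hold against descriptive comparison of phenotypes by severity, and it does not show that any particular finding will be spurious.

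The size is conditional on the assumed age SD, age gap and correlation. Over gaps of 10 to 20 years, Mann-Whitney rejects in about 8% to 69% of trials when nothing but age differs; with no age gap it stays near 5%. Comorbidity and sex were not quantified. The direction of the argument is the same for them, and for comorbidity it is strongest against controls selected to have none.

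**What to change.** Keep Mann-Whitney, ANOVA and Pearson as descriptive, and make adjusted models the main analysis for the three inferences above.

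1. **Markers among COVID-19 patients.** Linear model on a log or rank scale with severity group, age, sex, comorbidity and CMV serostatus. CMV serology is planned only for patients, so this term belongs only here.
2. **Patient-control contrasts.** Adjust for age and sex only. A CMV term would drop every control, and a comorbidity term would rest on extrapolation because no control has chronic disease. Add a sensitivity analysis limited to patients without chronic disease.
3. **Protective factors.** Multinomial, or pairwise binary, logistic regression of severity group on vaccination history and comorbidities together, with age and sex. A proportional-odds model is less suitable: the categories are filled to about 30 each, and its estimates are not preserved under sampling by outcome. Comorbidities are themselves candidate factors in the Secondary Objectives, so report their estimates too.
4. **Time since vaccination.** If it is nearly collinear with age, report that its effect cannot be separated from age.

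Enrolment is complete, so matching is no longer available, but the immunological analysis is described as ongoing and the wording can still change. Age, sex, comorbidity and patient CMV status should already be in the data set, so no new collection is needed. The cost is wider intervals where groups overlap little in age (variance factor 1.11 to 1.44 at gaps of 10 to 20 years, before any gain from age explaining residual variance). The multinomial model must also be kept small: four single-term covariates already need 4 × 3 = 12 slopes and 3 intercepts on 120 patients.
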